## Abstract

**Background:**

Approximately 55,000 children in New Zealand do not eat breakfast on any given day. Regular breakfast skipping has been associated with poor diets, higher body mass index, and adverse effects on children's behaviour and academic performance. Research suggests that regular breakfast consumption can improve academic performance, nutrition and behaviour. This paper describes the protocol for a stepped wedge cluster randomised trial of a free school breakfast programme. The aim of the trial is to determine the effects of the breakfast intervention on school attendance, achievement, psychosocial function, dietary habits and food security.

**Methods/Design:**

Sixteen primary schools in the North Island of New Zealand will be randomised in a sequential stepped wedge design to a free before-school breakfast programme consisting of non-sugar coated breakfast cereal, milk products, and/or toast and spreads. Four hundred children aged 5-13 years (approximately 25 per school) will be recruited. Data collection will be undertaken once each school term over the 2010 school year (February to December). The primary trial outcome is school attendance, defined as the proportion of students achieving an attendance rate of 95% or higher. Secondary outcomes are academic achievement (literacy, numeracy, self-reported grades), sense of belonging at school, psychosocial function, dietary habits, and food security. A concurrent process evaluation seeks information on parents', schools' and providers' perspectives of the breakfast programme.

**Discussion:**

This randomised controlled trial will provide robust evidence of the effects of a school breakfast programme on students' attendance, achievement and nutrition. Furthermore the study provides an excellent example of the feasibility and value of the stepped wedge trial design in evaluating pragmatic public health intervention programmes.

**Trial Registration Number:**

Australian New Zealand Clinical Trials Registry (ANZCTR) - ACTRN12609000854235

## Background

Up to one-fifth of New Zealand children leave for school without eating breakfast [1-3]. Missing breakfast is more common amongst older children, girls, Māori and Pacific children, and those living in lower socioeconomically resourced areas [2,3]. Missing breakfast has been associated with adverse effects on cognitive function (including memory), academic performance, school attendance, psychosocial function and mood in children and young people [4,5]. Conversely, breakfast consumption is associated with a range of positive outcomes, including better school attendance, academic performance, nutrient intake, fitness, and healthier body weight [6-8].

Breakfast contributes substantially to daily energy and nutrient intake. Breakfast provides 16% of New Zealand children's daily energy intake, around one-third of calcium, iron, thiamine, riboflavin and folate intakes, and one-fifth of zinc intake [9]. Children who miss breakfast have significantly worse daily nutrient intakes, including higher intakes of total fat, and lower intakes of dietary fibre and micronutrients than those who eat breakfast [9]. Hungry children may lack the energy and motivation to become involved in classroom activities [10], while malnutrition and micronutrient deficiencies have been shown to impact on physical, mental, and social health, and reduce cognitive functioning [11-13].

A number of countries (e.g. United States, United Kingdom, Sweden) have government or non-government funded school breakfast programmes, which aim to provide a free healthy breakfast to children and thereby improve nutrition and academic outcomes [14-16]. In New Zealand, some school breakfast programmes have been introduced in recent years, although none are official government programmes. The Red Cross Breakfast in Schools programme, which is available to decile 1 primary schools (areas of low socioeconomic resource), was established in 2007 [17]. The programme is run with support from Countdown supermarkets (Progressive Enterprises) who supply breakfast foods free of charge. In 2008, the KickStart Breakfast programme for decile 1-4 schools (areas of low to moderate socioeconomic resource) was launched by Fonterra Co-Operative Group Limited and Sanitarium Health Food Company.

Research indicates that school breakfast programmes have benefits in relation to nutrition, school attendance, academic performance and psychosocial function [14,18]. However, findings have been inconsistent, limited by poor study design and methods, and frequently confuse correlation with causation. A Cochrane review identified seven randomised, controlled trials investigating the effects of school feeding programmes (breakfast, lunch or snacks) [18]. However, only two were undertaken in high income countries, one of which experienced substantial contamination between trial intervention groups [19], whilst the other did not include a full school breakfast (just milk) [20]. Based on all studies, the Cochrane review concluded that there is a dearth of high quality evidence on school feeding programmes and recommended further well-designed studies, particularly cluster randomised controlled trials [18].

This paper presents the study protocol for a stepped wedge cluster randomised controlled trial to investigate the effects of a free school breakfast programme on students' school attendance, academic achievement, psychosocial function, dietary habits and food security.

## Method/Design

In New Zealand, there are two stages of schooling: primary (years 0-8) and secondary (years 9-15). Primary schools include full primary (years 0-8), contributing (years 0-6) and intermediate (years 7-8) schools. There are four terms in a primary school year, with term 1 starting in early February and term 4 ending in December. All schools are assigned a decile rating, which indicates the extent to which the school draws its students from a range of socioeconomic areas. Decile 1 schools are the 10% of schools with the highest proportion of students from low socioeconomic resource areas (defined according to residents' income, occupation, household crowding, educational qualifications and income support) and decile 10 are the 10% of schools with the highest proportion of students from high socioeconomic areas.

### Design

The study is a stepped wedge cluster randomised controlled trial in which participating schools (clusters) cross over from control to intervention phase (i.e. one-way switch over) at different time points throughout the school year. The order of switch-over ('sequence') is determined randomly for each group of clusters, and all clusters receive the breakfast programme intervention by the end of study (Figure 1). All schools start the trial at the same time point and act as controls until such time as they are randomised to crossover from control to intervention. The stepped wedge design is suitable for a phased evaluation approach, where the intervention is likely to do more good than harm, thus making it unethical to completely withhold the intervention from a control group, and/or where it is not possible to start delivery of the intervention to all participants at the same time [21]. Both of these criteria apply in this trial. Data on all individual study participants are collected once each school term over the entire school year.

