### Study sample

Eligible schools are decile 1-4 primary schools (students aged 5-13 years) located in selected regions (Auckland, Northland, Waikato, Wellington) in the North Island of New Zealand. To take part in the study, schools must not have an existing breakfast programme and must agree to start one in the 2010 school year. Schools must be of sufficient size that they estimate at least 25 students would attend the breakfast programme each day.

Eligible participants are students aged 5-13 years who plan to attend the school breakfast club at least occasionally and do not have a diagnosed food allergy. Only one child per household may take part. Recruitment involves researchers and/or the school principal briefly outlining the study during a regular school assembly or classroom talks and answering any questions children have. Those interested in taking part in the study are asked to register their interest and take a study information pack home to their parents/caregivers. The study pack includes participant information, a consent form for parents, an assent form for children, forms to collect demographic information (e.g., age, sex and ethnicity of the child, household income) and parents' contact details, and an envelope in which to return completed forms. Students return completed forms to their teacher or the school office, and these are collected by researchers.

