### Sample size calculations

The target sample size is a total of 16 schools (four schools per sequence) with an average 25 students per school, i.e. a total of 400. Assuming an intra-cluster coefficient (ICC) of 0.05, this sample size will provide at least 85% power, with a significance level of α = 0.05, to detect a 10% absolute increase in the proportion of students with a school attendance rate of 95% or higher.

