### Randomisation and blinding

Schools are randomly allocated to one of the four sequences for time of crossover from control to intervention phase using a computer-generated list of random numbers. The allocation sequence is overseen by the study statistician (YJ). Consideration is given to school decile and school type in order to reduce the potential imbalance between sequences. Due to the nature of the study intervention it is not possible to blind participants, breakfast providers, or outcome assessors. However, choice of an objective primary outcome (school attendance using routinely collected data from schools) should minimise risk of bias.

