### Statistical analysis

Treatment evaluations will be performed according to the principle of intention-to-treat (ITT), using data collected from individual trial participants at randomised schools. Schools will be treated as clusters in the analysis because participant data collected from the same school are likely to be more correlated than those collected from different schools. Furthermore, in a stepped wedge design, information is collected repeatedly on each participant over the control and intervention periods. Advanced statistical methods appropriate for this type of study design will therefore be used. Generalised Linear Mixed models will be used to adjust for the effect of clustering and repeated measures over time. Intra cluster correlation (ICC) coefficients will be re-evaluated using the study data. Unidirectional crossover as well as any potential secular trends may be incorporated with a time effect. A pre-specified analysis plan outlines detailed statistical methods.

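### Four sequences measured in only four terms leave at least one sequence (4 of 16 schools) without a full measured term in one phase; one prior term of attendance would supply it cheaply

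*Protocol article*

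**What the plan says.** The layout is spread over several sections of the protocol article.

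- **Sequences** (Randomisation and blinding): "Schools are randomly allocated to one of the four sequences for time of crossover from control to intervention phase".
- **Size** (Sample size calculations): "The target sample size is a total of 16 schools (four schools per sequence) with an average 25 students per school".
- **Periods** (Method/Design): "There are four terms in a primary school year, with term 1 starting in early February and term 4 ending in December".
- **Measurements** (Abstract, Methods/Design): "Data collection will be undertaken once each school term over the 2010 school year (February to December"). The Design section repeats this frequency, and no assessment before term 1 is described.
- **Start and end states** (Design): "All schools start the trial at the same time point and act as controls until such time as they are randomised to crossover". The same section says that every cluster has received the programme by the end of the study.
- **Data per child** (Statistical analysis): in a stepped wedge design, "information is collected repeatedly on each participant over the control and intervention periods".

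The Primary outcome section judges attendance as a rate per term. It comes from half-day records that schools keep routinely and that are extracted at the end of each term.

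**The concern.** For every sequence to be measured in both phases, there must be more measurement periods than distinct crossover times. Here the two numbers are equal. A reader of the Design and Statistical analysis sections would expect each child to supply at least one control term and one intervention term, and for a quarter of the children the stated schedule cannot deliver that.

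The affected sequence contributes no before/after contrast. It still helps to estimate the period effects and the between-school comparison, but the effect is estimated less precisely than it could be. For attendance the missing information may already sit in school registers, so the loss may be avoidable at little cost.

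**Working it through.** **1. Counting.** Four ordered measurements have 4 - 1 = 3 gaps. A school has a full term in both phases only if it switches in one of those gaps. Four distinct crossover times do not fit into three gaps, so at least one sequence switches at or before the first term (no control term) or too late for a full intervention term. That is 4/16 schools and 4 x 25 = 100 of 400 children (25%). Because all schools end on the programme, the likelier layout, with rows as sequences and columns as terms, is `1111 / 0111 / 0011 / 0001`. It has 6 control cells of 16 (37.5%).

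**2. The plan's own power figure.** The stated power of at least 85% cannot be reproduced, because no control proportion is given. For the 4x4 layout with no within-child correlation, cluster autocorrelation 0.8 or 1, two-sided alpha 0.05 and control proportions 0.30-0.85, computed power runs from 62% to 98.5%. The comparison below is therefore relative: the same trial with and without one extra period.

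**3. Model.** Generalised least squares on school-term means with fixed term effects. From the protocol: 16 schools, m = 25, ICC 0.05. Assumed: total variance 0.5 x 0.5 = 0.25 (control proportion 50%), cluster autocorrelation 0.8-1, within-child correlation 0-0.7.

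With cluster autocorrelation 1 the standard stepped-wedge formula applies:

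Var = I s²(s² + T t²) / [(I U - W) s² + (U² + I T U - T W - I V) t²]

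Here I is the number of schools and T the number of periods. U is the number of treated school-terms, W the sum of squared treated counts per term, and V the sum of squared treated counts per school. The variance of a school-term mean splits into a part s² that is new each term and a part t² that persists.

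**4. Example with within-child correlation 0.5.**

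- School component: 0.05 x 0.25 = 0.0125.
- Child component of a mean: 0.95 x 0.25 / 25 = 0.0095, half of it persistent.
- So s² = 0.00475 and t² = 0.0125 + 0.00475 = 0.01725.
- In both layouts U = 40, W = 480, V = 120.

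*Four terms (T = 4):* I U - W = 160, and the second bracket is 1600 + 2560 - 1920 - 1920 = 320. Var = 0.076 x 0.07375 / (0.76 + 5.52) = 0.000893, so SE = 2.99 percentage points.

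*One leading all-control period added (T = 5):* the first bracket stays 160 and the second is 1600 + 3200 - 2400 - 1920 = 480. Var = 0.076 x 0.0910 / (0.76 + 8.28) = 0.000765, so SE = 2.77 points.

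Reduction: 1 - 0.000765/0.000893 = 14.3%. Control cells rise to 10 of 20 (50%).

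**5. Range of the variance reduction.**

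| Within-child correlation | Cluster autocorrelation 1 | Cluster autocorrelation 0.8 |
|---|---|---|
| 0 | 11.2% | 9.2% |
| 0.3 | 13.1% | 11.4% |
| 0.5 | 14.3% | 12.8% |
| 0.7 | 15.3% | 13.9% |

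A cut of 9.2-15.3% equals 1/(1 - 0.092) to 1/(1 - 0.153), or about 10-18% more schools. These figures assume a complete prior-term record for every child.

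**6. Mirror layout.** If instead the last sequence is never measured on the programme (`0111 / 0011 / 0001 / 0000`), then U = 24, W = 224, V = 56. The brackets are again 160 and 576 + 1536 - 896 - 896 = 320, so the variance is identical. The gain does not depend on which end of the wedge is short.

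**The case against.** **The layout is inferred.** Figure 1 was not available, and the text says only that schools switch at different times in the year. This stands in part. Attendance is kept by half day, so a switch within term 1 would leave the first sequence some pre-programme half-days. A reader might infer that this sequence has no pre-programme attendance at all, and the text does not establish that. It does fix one measurement per term and a per-term rate, and it describes no splitting of a term, so the count of full measured terms is unaffected.

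**The Statistical analysis sentence is general.** It explains why repeated measures need modelling and does not promise both phases for every child. That is fair. It is loose wording to clarify, not a false claim about this trial.

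**The design is valid.** A reader might infer that a sequence without a control term biases or invalidates the result. The documents do not support that. Schools are randomised, with decile and school type considered, and the effect is identified from same-term comparisons plus the changes in the other sequences.

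**The stated power may be met anyway.** In the example above power is about 92% with four periods and 95% with five. Other assumptions differ. With no within-child correlation and cluster autocorrelation 1, power goes from 81.4% to 85.7% at a control proportion of 0.70. At a control proportion of 0.50, with cluster autocorrelation 0.8 and within-child correlation 0.3, it goes from about 71% to 76%, still short of 85%. The protocol's inputs do not decide between these cases, so a missed power target is not shown.

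**The remedy rests on records that are not described.** That 2009 attendance can be extracted is an inference from routine recording. Missing records would also depend on age and school type.

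**Parent-reported outcomes.** The recruitment pack includes "forms to collect demographic information (e.g., age, sex and ethnicity of the child, household income"), an open list, and its timing relative to the clubs opening is not given. A reader might infer that these outcomes have no pre-programme value. The text neither shows nor excludes that.

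**This is a condensed article.** Step dates and use of prior attendance could be in the full protocol or analysis plan. The count, however, follows from design features that the article itself states.

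**Conclusion.** The point holds as one of efficiency and clarity. The stated numbers of sequences, terms and collections mean that at least one sequence, a quarter of the schools and children, has no full measured term in one phase. Since all schools finish on the programme, this is probably the control phase of the first sequence.

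The consequence is lost precision and lost within-child comparison, not bias. A common all-control period would reduce the variance of the effect by about 9-15%. That rests on an ICC of 0.05 from the protocol, the assumed correlation ranges above, and complete records; incomplete records give less. The proportional gain does not depend on the unstated control proportion, which scales both variances alike. This is a worthwhile, cheap improvement, and the trial does not fail without it.

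**What to change.** 1. Where the schools' routine registers allow, extract term 4, 2009 attendance for consented children, compute the same 95% indicator, and enter it as a common all-control period in the primary mixed model with period effects. Participating schools must have no existing breakfast programme, which supports treating that term as control. Cost: one extra export per school and one line in the consent form. Downside: new entrants, and children who changed school (for example into an intermediate school), would have no record there and would contribute four terms only.
2. Reword the Design and Statistical analysis sections to say which sequence lacks which phase within the four 2010 terms, and when in a term schools switch. Cost: two sentences.
3. Optional: collect the parents' breakfast questions and the CCHIP scale before any club opens, for instance in the recruitment pack. This depends on recruitment timing, which is not stated, and the attendance extract does not replace it.

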**Figure 1 F1:**
[figure not shown]
**Stepped wedge cluster randomised trial design**.

### Aims

The primary aim is to investigate the effects of a school breakfast programme in low decile schools on students' attendance. Secondary aims include examination of the impact of the school breakfast programme on students' school achievement, psychosocial function and nutrition.

### Study sample

Eligible schools are decile 1-4 primary schools (students aged 5-13 years) located in selected regions (Auckland, Northland, Waikato, Wellington) in the North Island of New Zealand. To take part in the study, schools must not have an existing breakfast programme and must agree to start one in the 2010 school year. Schools must be of sufficient size that they estimate at least 25 students would attend the breakfast programme each day.

Eligible participants are students aged 5-13 years who plan to attend the school breakfast club at least occasionally and do not have a diagnosed food allergy. Only one child per household may take part. Recruitment involves researchers and/or the school principal briefly outlining the study during a regular school assembly or classroom talks and answering any questions children have. Those interested in taking part in the study are asked to register their interest and take a study information pack home to their parents/caregivers. The study pack includes participant information, a consent form for parents, an assent form for children, forms to collect demographic information (e.g., age, sex and ethnicity of the child, household income) and parents' contact details, and an envelope in which to return completed forms. Students return completed forms to their teacher or the school office, and these are collected by researchers.

### Sample size calculations

The target sample size is a total of 16 schools (four schools per sequence) with an average 25 students per school, i.e. a total of 400. Assuming an intra-cluster coefficient (ICC) of 0.05, this sample size will provide at least 85% power, with a significance level of α = 0.05, to detect a 10% absolute increase in the proportion of students with a school attendance rate of 95% or higher.

### Ethics approval

Ethical approval for the trial was received from the Northern Y Regional Ethics Committee (Reference: NTY/09/09/084).

### Randomisation and blinding

Schools are randomly allocated to one of the four sequences for time of crossover from control to intervention phase using a computer-generated list of random numbers. The allocation sequence is overseen by the study statistician (YJ). Consideration is given to school decile and school type in order to reduce the potential imbalance between sequences. Due to the nature of the study intervention it is not possible to blind participants, breakfast providers, or outcome assessors. However, choice of an objective primary outcome (school attendance using routinely collected data from schools) should minimise risk of bias.

### Intervention

The intervention is a free daily before-school breakfast programme; either the Red Cross Breakfast in Schools programme or an unbranded school breakfast programme provided by Fonterra and Sanitarium.

The Red Cross Breakfast in Schools programme is available to decile 1 primary schools. Food is provided free of charge by Countdown supermarkets (Progressive Enterprises Ltd). Schools select from a list of foods that includes breakfast cereal (wheat biscuits), milk, bread, spreads (margarine, jam, honey, Marmite), Milo (chocolate flavoured drink powder), milk powder and sugar. Food is delivered weekly. During the trial the programme is set up and run as usual through the Red Cross, with schools responsible for finding volunteers to run the programme and Red Cross providing assistance and training. The unbranded school breakfast programme is available to decile 1-4 primary and intermediate schools. Food is provided by Fonterra Co-operative Group Limited (fresh or UHT milk) and Sanitarium Health Food Company (Weet-Bix). Milk is provided weekly (where fresh milk is supplied) and Weet-Bix and UHT milk delivered each term. During the trial the programme is set up and run as usual, with schools providing volunteers to run the breakfast programme.

Schools are provided with information on how to set up and run a breakfast club, but are responsible for finding a suitable venue, equipment and volunteers to run the breakfast club. Schools are offered NZ$1000 as reimbursement for their participation in the trial, and this may be used to help set up the breakfast club or for other purposes. No attempts are made to standardise the intervention or its delivery in individual schools.

